#### 2.4.2 Secondary outcomes

The secondary outcomes encompass physiological indicators such as blood pressure and blood lipid profiles (including triglycerides, low-density lipoprotein (LDL), high-density lipoprotein (HDL), and very-low-density lipoprotein (VLDL) cholesterol levels), quality of life assessments, mental health evaluations, and lifestyle factors (dietary habits and physical exercise patterns). Secondary outcome measures (such as blood pressure, lipid levels, and quality of life) will be analyzed using multiple linear regression or logistic regression, controlling for confounding factors such as age and baseline BMI, to assess the independent effects of the interventions. Subgroup analysis will further explore the differences in intervention effects across subgroups defined by factors such as age and BMI classification, with interaction tests conducted to verify the robustness of the results.

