#### 2.1.1 Sample size

As this study is a randomized controlled trial, the respondents will be divided into manual intervention group, artificial intelligence (AI) intervention group, artificial intelligence and manual combined intervention group, and observe the BMI of pregnant women, maternal weight and maternal adverse pregnancy outcomes as the main outcome indicators. The sample size was calculated based on an expected effect size of 0.5, which corresponds to the minimal clinically important difference (MCID) of the primary outcome. This MCID was determined based on previous literature and clinical judgment. Setting bilateral α = 0.05, the degree of certainty was 90%. Using the PASS15 software, we obtained a sample size of N1 = 40 cases for the group and N2 = 40 cases for the group and N3 = 40 cases for the group. For a total of at least 120 subjects to be included in the study.

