### 2.2 Randomization

After recruitment, the research team will conduct a pre-enrollment assessment and post-enrollment informed consent with the participants and their families, followed by randomization grouping:

A comprehensive assessment will be conducted before the participants are enrolled, including structured questionnaires and clinical examinations.

The approved subjects were randomly divided into Manual intervention group, artificial intelligence intervention group (AI intervention group), artificial intelligence and artificial combined intervention group (AI & Manual intervention group). The specific randomization operation is as follows: This study uses a simple randomization method. Random number series were randomly generated by the study designer using the RANDBETWEEN formula in EXCEL. The project will divide the subjects into different groups according to the sequence, the intervention team will know the grouping results, and the subjects will not know the grouping results.

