Social and demographic factors	Family related factors	Survey	Parents' medical history of hypertension, diabetes, and cardiovascular disease, annual family income	√					
Health status		Survey and Medical record	Height, weight, BMI, blood pressure and blood sugar, smoking and drinking status, WHO−5	√	√	√	√	√	√
Activity	Physical activities	Survey	Physical Activity Rating Scale-3, PARS-3	√	√	√	√	√	√
Psychosocial status	Quality of life	Survey	EQ-5D version, EQ-5D-5L	√	√	√	√	√	√
	Sleep	Survey	Pittsburgh sleep quality index, PSQI	√	√	√	√	√	√
	Social support	Survey	Social support rate scale, PSSS-SF	√	√	√	√	√	√
Psychology status	Anxiety	Survey	General Anxiety Disorder-7, GAD-7	√	√	√	√	√	√
	Stress	Survey	Perceived Stress Scale, PSS-4	√	√	√	√	√	√
	Self-efficacy	Survey	General Self-Efficacy Scale	√	√	√	√	√	√
	Family health	Survey	The Family Health Scale short-form, FHS-SF	√	√	√	√	√	√
Cost-effectiveness	Tracking cost	Survey and medical record		√	√	√	√	√	√
Qualitative results			Effect of trial	√	√	√	√	√	√

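### Section 2.4.2 names age and baseline BMI as example covariates for the secondary outcomes but not each outcome's own T-0 value, which Table 1 collects for most of them; naming it would gain precision at almost no cost

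*Protocol article*

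**What the plan says.** Section 2.4.2 assigns the secondary outcomes to regression: they "will be analyzed using multiple linear regression or logistic regression, controlling for confounding factors such as age and baseline BMI". The covariates are introduced as examples, so the list is open. The stated reason for including them is confounding.

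Table 1 (section 2.5) ticks T-0 and every later time point for the row "Height, weight, BMI, blood pressure and blood sugar, smoking and drinking status, WHO−5" and for "General Anxiety Disorder-7, GAD-7". It does the same for EQ-5D-5L, PSQI, PARS-3, PSS-4, self-efficacy, social support and family health. T-0 is read here as the baseline assessment. Lipids and diet are secondary outcomes in section 2.4.2, but Table 1 has no row for either.

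On allocation, section 2.2 states: "This study uses a simple randomization method". Section 2.1.1 gives the arm sizes as "N1 = 40 cases for the group and N2 = 40 cases for the group and N3 = 40 cases for the group".

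Section 2.6 calls GEE the main analysis. It adds time-by-group interaction terms, with baseline as one of the times, in the sentence that introduces the socioeconomic subgroup analyses.

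**The concern.** In a randomised comparison, covariates are not needed to remove confounding. They serve to remove prognostic variance and to correct for chance imbalance. For a follow-up GAD-7, EQ-5D-5L or blood pressure value, the strongest predictor is normally the same measure at T-0. Section 2.4.2 picks its example covariates on a confounding rationale and does not point to that predictor. An analyst could follow the text and leave it out.

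Two things are then lost. The standard error of each affected arm contrast is wider than the collected data allow. And a chance difference between arms at T-0 passes into the follow-up contrast, where it can look like an intervention effect or hide one. Unstratified simple randomisation with 40 per arm makes such differences fairly common.

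**Working it through.** **Inputs from the article.** Three arms of 40. Section 2.1.1: "The sample size was calculated based on an expected effect size of 0.5", stated for the primary outcome; "Setting bilateral α = 0.05, the degree of certainty was 90" per cent.

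**Inputs assumed.** The article gives no effect size or SD for any secondary outcome, and no baseline-to-follow-up correlation. I borrow 0.5 as a standardised difference for a pairwise contrast and vary the correlation ρ.

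**The plan's own figure.** For two means, n = 2(1.960 + 1.282)² / 0.5² = 84.06, so 85 per arm, not 40. The 40 per arm therefore does not reproduce under this reading. That is a separate matter; here it only fixes the starting power.

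**Power without the own baseline.** The standard error is √(2/40) = 0.224 SD. With d = 0.5 and two-sided α = 0.05, the noncentral t gives 59.8% (normal approximation 60.9%).

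**Power with the own baseline.** The residual SD falls from 1 to √(1 − ρ²), so the effective difference is 0.5/√(1 − ρ²). For comparison, the change-from-baseline contrast has SD √(2(1 − ρ)). Noncentral t results:

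| Assumed ρ | √(1 − ρ²) | Reduction in SE | Power, own baseline omitted | Power, own baseline as covariate | Gain (points) | Power, change contrast |
|---|---|---|---|---|---|---|
| 0.3 | 0.954 | 5% | 60% | 64% | 4 | 46% |
| 0.5 | 0.866 | 13% | 60% | 72% | 12 | 60% |
| 0.7 | 0.714 | 29% | 60% | 87% | 27 | 81% |

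Over the wider range ρ = 0.2 to 0.8, the gain runs from 1.8 to about 35 points.

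A simulation of the three-arm regression agreed. It used 6,000 trials per setting, with arm, age and baseline BMI in the model and an assumed correlation of 0.2 between BMI and the outcome at baseline. Power without and with the own baseline was 0.601 and 0.637, 0.596 and 0.724, and 0.605 and 0.874.

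**Chance imbalance.** The difference between two arm means at T-0 has SD 0.224. The probability that it exceeds 0.3 SD in either direction is 2[1 − Φ(0.3/0.224)] = 2[1 − Φ(1.34)] ≈ 18% for a given pair of arms. Among null trials with such an imbalance, the simulation rejected in 6.7%, 10.0% and 15.1% (ρ = 0.3, 0.5, 0.7) without the own baseline, and in 4.7%, 4.9% and 4.6% with it. A simpler two-arm normal calculation gives 7.5%, 12% and 18% without it, the same pattern. Over all randomisations the rate stays near 5% either way.

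**Change contrast against covariate.** The variance ratio is (1 − ρ²) / [2(1 − ρ)] = (1 + ρ)/2, which never exceeds 1. A change contrast is therefore never more efficient than adjustment for the own baseline.

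**The case against.** The best defence has four parts.

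- **The list is open.** Section 2.4.2 gives examples, so it neither names nor excludes the own baseline, and a condensed article may leave the full list to an analysis plan. This stands against the reading that the plan adjusts for age and baseline BMI only; the text does not say that. It does not remove the point: the article chose which covariates to illustrate and why, and that rationale leads towards confounders and away from the most useful prognostic variable.
- **Section 2.6 plans a GEE that uses every measurement.** Baseline is a time level there, and the sentence covers physiological outcomes and health behaviours, which overlap the secondary outcomes. A reader might infer from section 2.4.2 that the within-woman pairing is thrown away throughout the plan. Section 2.6 does not support that. But those interaction terms are introduced for subgroup analyses and are not said to replace the section 2.4.2 model. With complete data they give a change contrast, which is at best as efficient as the covariate.
- **Not every secondary outcome is affected.** Table 1 shows no T-0 value for lipids or diet. This stands.
- **The imbalance figures are conditional.** They describe about 18% of randomisations for one pair of arms. This also stands: the unconditional error rate is intact, and nothing here shows bias.

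**Conclusion.** The point holds as a matter of efficiency. For secondary outcomes with a T-0 value in Table 1, a model with only the named covariates is less precise than the data allow and leaves chance baseline imbalance in the arm contrasts.

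The size depends on the correlation. The gain in power is about 4 to 27 points for ρ from 0.3 to 0.7, for a continuous outcome with 40 per arm and a difference of 0.5 SD. A reader might fasten on the 12-point figure as the loss, but it belongs to an assumed ρ of 0.5, and the article supplies neither that correlation nor a secondary effect size. Nothing was computed for the logistic models, and these figures should not be applied to them.

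This is worth correcting because the remedy is so cheap, but it does not threaten the validity of the secondary analyses.

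**What to change.** In section 2.4.2, replace the covariate clause with: *Each secondary outcome measured at T-0 will be analysed with its own T-0 value as a covariate, together with age and baseline BMI.* Where the model is logistic, enter the T-0 value of the underlying measure. The same section should say how this regression relates to the GEE in section 2.6: which of the two gives the reported result for each secondary outcome, and how baseline enters the GEE.

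The cost is one degree of freedom per model and a simple rule for women whose T-0 value is missing, such as mean imputation of the baseline covariate. For outcomes with a T-0 value in Table 1, no new data, visits or participants are needed.

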**Results:**

The study will evaluate the effects of health interventions on obese pregnant women through primary outcomes (e.g., BMI, weight, adverse pregnancy outcomes) and secondary outcomes (e.g., physiological indicators, quality of life, mental health) using various statistical methods. The results will provide insights into the intervention's effectiveness and cost-effectiveness across different socioeconomic groups.

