### 2.6 Statistical analysis

Participants' socio-demographics are presented as count and proportion, and the χ^2^ test was used to assess categorical variables. The continuous variables normally distributed were assessed by the student's *t*-test. The Fisher's exact or the chi-square test was adopted for categorical data, and statistical significance was set at *p* < 0.05. The main analysis was performed using generalized estimating equations (GEE) model. The GEE solved the problem of correlation of longitudinal data, utilizing the results of each measurement in the longitudinal data, which greatly reduces the loss of information (20). To clarify whether socioeconomic status affects the effectiveness of ILSM, we conducted several subgroup analyses for physiological health outcomes and health behaviors, and added the interaction terms to generalized estimating equations model to assess the interactions between time (at baseline, 3-month, 6-month, and 18-month) and group (intervention and control). We also used GEE to analyze the health benefits of intervention and control groups among participants with different socioeconomic status. Significance level of the associations in the final model was set at *P*-value 0.05. The data were analyzed using SPSS 20.0 (IBM Corporation, Armonk, NY, USA).

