Next are the differences with the existing literature. Notably, our cost-benefit analysis revealed that the AI-only intervention offered a scalable solution with moderate efficacy, whereas the combined AI+Manual group achieved the highest clinical impact. This contrasts with Perdomo et al., who emphasized surgical and pharmacological interventions as primary strategies for severe obesity (15). However, our results align with Sallam et al., where TLC combined with medication synergistically improved metabolic outcomes (20). Such parallels suggest that hybrid models (AI + human expertise) may bridge the gap between resource-intensive and purely automated interventions.

However, this study has the following limitations. First, despite the high coverage rate of smartphones in China, some patients may not be able to use them well, which may hinder the implementation and reduce the effectiveness of AI interventions. Second, for the collection of the primary and secondary outcomes, we primarily used questionnaire indicators, which may inevitably lead to recall bias. Third, due to the lack of balanced stratification, comparative analyses between subgroups may not be suitable if the sample size of each group is insufficient across groups (e.g., compare the differences and potential influencing factors of AI-TLC intervention effects in different age groups). Fourth, the short-term follow-up period (up to 3 months postpartum) precludes conclusions about long-term weight maintenance. Meta-analyses of lifestyle interventions for obese pregnant women indicate that postpartum weight retention remains a challenge beyond 12 months (35), emphasizing the need for extended follow-up in future studies. Additionally, socioeconomic disparities in AI accessibility—particularly among older or rural populations—may limit generalizability, necessitating stratified analyses in broader cohorts.

Despite these limitations, this study may provide a scientific basis for developing personalized and effective interventions to further improve the health behavior and health of obesity pregnant women. It is expected to provide a new perspective and effective approach to the management of obesity pregnant women.

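### Socioeconomic effect modification is to be judged from separate stratum analyses at 0.05, with interaction tests as a robustness check; these and the secondary outcomes should be reported as exploratory estimates

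*Protocol article*

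**What the plan says.** Section 2.6 fixes one threshold: "Significance level of the associations in the final model was set at *P*-value 0.05". To find out whether socioeconomic status changes the intervention's effectiveness, it plans several subgroup analyses of physiological outcomes and health behaviours, plus GEE models of benefit within women of different socioeconomic status. The interaction it describes is between time and group. No term for group by socioeconomic status is named.

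Section 2.4.2 says that the secondary outcomes are analysed by linear or logistic regression, "controlling for confounding factors such as age and baseline BMI, to assess the independent effects of the interventions". Subgroup analyses by factors such as age and BMI class are described as exploring differences, "with interaction tests conducted to verify the robustness of the results".

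Two other places set expectations. The Results paragraph of the abstract says: "The results will provide insights into the intervention's effectiveness and cost-effectiveness across different socioeconomic groups". The limitations in section 3 concede that "comparative analyses between subgroups may not be suitable if the sample size of each group is insufficient across groups".

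Section 2.1.1 gives the size: "N1 = 40 cases for the group and N2 = 40 cases for the group and N3 = 40 cases for the group".

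**The concern.** Whether an intervention works differently in two groups is a question about the difference between two effects, and the interaction between arm and subgroup estimates that difference. The text puts other things in its place. In section 2.6 the socioeconomic question is answered stratum by stratum, with an interaction that concerns only time and arm. In section 2.4.2 interaction tests are planned, but as confirmation of results reached some other way. Read literally, a p-value below 0.05 in one stratum and above it in another could be reported as effect modification.

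The secondary outcomes raise a related issue. They are numerous, each is analysed for an effect, and the same 0.05 applies to each. The primary question in section 1 asks about health behaviours as well as health outcomes, yet diet and exercise appear only among the secondary outcomes. The behavioural half of the answer would therefore come from this family. At stake is whether an isolated small p-value becomes a statement that the intervention works, or works for one kind of woman.

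**Working it through.** **The plan's own figure.** Section 2.1.1 gives 40 per arm for an effect size of 0.5, two-sided 0.05 and 90% power. Taking 0.5 in SD units (the metric is not named), a two-arm comparison needs n = 2(1.96 + 1.2816)² / 0.5² = 84.1, so 85 per arm. The 40 does not reproduce. That is a separate matter; the checks below take 40 per arm as stated. The plan states no familywise error rate to reproduce.

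**Power for a subgroup difference.** Assumptions: a binary modifier split 50/50, SD 1, one contrast between two arms, normal approximation. Each arm-by-stratum cell then has 20 women.

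- SE of the difference between two stratum effects = √(4/20) = 0.447 SD.
- For a true difference of 0.5 SD: 0.5/0.447 = 1.118, and power ≈ Φ(1.118 − 1.96) = Φ(−0.842) = 0.20.
- Difference needed for 80% power = (1.96 + 0.842) × 0.447 = 1.25 SD.

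**What stratum-by-stratum testing shows when there is no effect modification.** Same assumptions, with the same true effect of 0.5 SD in both strata.

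- SE within a stratum = √(2/20) = 0.316 SD; 0.5/0.316 = 1.581; power ≈ Φ(1.581 − 1.96) = Φ(−0.379) ≈ 0.35.
- Chance that exactly one of the two strata is significant = 2 × 0.35 × 0.65 ≈ 0.46.
- With no effect in either stratum, that chance is 2 × 0.05 × 0.95 = 0.095.

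So an apparent contrast between strata would arise in nearly half of trials in which the effect is identical.

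**Secondary outcomes: the count.** Section 2.4.2 names blood pressure, four lipids, quality of life, mental health, diet and exercise: 9, or 10 if systolic and diastolic pressure are separate. Counting the individual scales in section 2.5 and Table 1 as outcomes gives about 15 to 17, but the article does not say that each is a secondary outcome.

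**Secondary outcomes: the false-positive chance.** For one independent test per outcome, it is 1 − 0.95^k: 0.40 for k = 10 and 0.54 for k = 15. For correlated outcomes and shared arms, it comes from a simulation of 20,000 trials with no true difference, three arms, equal correlation between outcomes and one visit. In the one-test columns, each pair gives a single contrast and an omnibus test.

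| Correlation | 10 outcomes, one test | 15 outcomes, one test | 10 outcomes, three contrasts | 15 outcomes, three contrasts |
|---|---|---|---|---|
| 0 | 40%, 40% | 53%, 54% | 73% | 86% |
| 0.3 | 35%, 35% | 46%, 47% | 65% | 78% |
| 0.5 | 29%, 30% | 36%, 37% | 57% | 67% |
| 0.7 | 22%, 23% | 26%, 28% | 44% | 51% |

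A separate run gave 42% for 15 outcomes with three contrasts at correlation 0.8. Tests at several visits, and subgroup tests, would add to these figures; their number is not given.

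**The case against.** The strongest reply is that this is a condensed article and the statistical analysis plan is not shown. Ordering of secondary outcomes, multiplicity control and subgroup reporting rules commonly sit there, so a missing hierarchy is not in itself a finding. That stands, and the point does not rest on it. It rests on what the article states: a flat threshold, stratum analyses as the route to the socioeconomic answer, and a confirmatory role for interaction tests. A later plan would have to reword these sentences rather than fill a gap.

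Second, the independent effects in section 2.4.2 may simply mean covariate-adjusted effects. That is a natural reading, and the sentence is not a claim of effectiveness for any one scale.

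Third, the authors may intend an arm-by-socioeconomic term, or may mean the interaction tests of section 2.4.2 to cover it. That is possible, but section 2.6 names only time and group, and section 2.4.2 still assigns interaction tests to robustness.

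Two stronger readings are tempting. A reader might infer that a false positive among the secondary outcomes is more likely than not. The documents do not support this without conditions: the count runs from about 9 to 17, no section fixes three pairwise contrasts for these outcomes (the three-way comparison appears in the cost-benefit sub-question, and section 2.6 speaks of two groups), and the correlation is unknown. Several plausible combinations fall below one half. A reader might also infer that no subgroup analysis is presented as exploratory. For age and BMI that is wrong: they are worded as exploration, with interaction tests, and the limitations add a caution.

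**Conclusion.** The concern holds in a limited form. The firm part is the route to subgroup conclusions: section 2.6 looks for socioeconomic effect modification by separate analyses without naming the relevant interaction, section 2.4.2 misplaces the role of interaction tests, and the abstract promises more than the limitations allow. Under an even split and an effect size in SD units, the trial has about 20% power for a 0.5 SD subgroup difference, and discordant significance between strata would be common without any true difference. An uneven split would lower the power further.

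The secondary-outcome part is conditional. Under no true difference, the chance of at least one p-value below 0.05 is about 36–54% for 15 outcomes with one test each (correlation 0.5 to 0), and about 44–86% for 10 to 15 outcomes with all three contrasts (correlation 0.7 to 0). These figures show why an isolated significant scale should not carry a claim of effectiveness. They are not a measured error rate of this plan.

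**What to change.** In sections 2.4.2 and 2.6, state that any difference by age, BMI class or socioeconomic status is judged only from the arm-by-subgroup interaction estimate (by time, where repeated measures are modelled) and its 95% confidence interval, never from significance within a stratum. Remove the wording that makes interaction tests a check of robustness, and name the group-by-socioeconomic-status term in the GEE model.

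In the same sections, say that secondary and subgroup results are exploratory, reported as estimates with 95% intervals, with no claim of effectiveness from p < 0.05 alone. In the abstract, replace the promise about socioeconomic groups with exploratory estimates by socioeconomic group.

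This needs no extra participants or data. The downside is that the sponsor gives up confirmatory claims from individual secondary scales and subgroups.
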